#### Secondary Outcomes

Average self-reported VR experience (NRS 0 [min]−10[max]) for the degree of realism, pleasure, and satisfaction with VR. These VR experience questions are assessed immediately following the laser procedure during the intervention visit.

Nurse-reported utility (binary [yes or no] questions of whether the nurse found VR-PAT to be helpful and easy to use during the procedure) is assessed immediately following the laser procedure at the intervention visit.

### Adverse Events and Oversight

Participants playing the VR-PAT game will be asked to answer the question, “Did the game make you feel not well? If yes, please explain.” Study coordinators will carefully review the collected data for any adverse events reported during the study intervention and will immediately report this information to the project manager. The principal investigators will determine how serious the event was, whether it was related, and if it was unexpected. All serious adverse events will be reported immediately to the sponsor and the IRB. During recruitment, participants will be informed of which simulator sickness symptoms to be aware of and advised that if they occur, the laser procedure can be paused to remove the headset and use the standard eye protection available. All participants will also receive a direct phone number for the research principal investigator to report adverse events.

This trial will be overseen and coordinated by the co–principal investigators and a project manager. We will have at least 1 researcher to assist with screening, recruitment, consent, and data collection. The research principal investigator and project manager meet weekly to discuss the project, including recruitment updates, challenges, and any reported adverse events. There is no specific steering committee for this study.

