## Introduction

### Background and Significance

Lasers have wide applications in medicine and dermatology. In pediatric patients, laser technology is often used to treat congenital and acquired skin conditions. Pulsed dye laser (PDL) is the standard of care for the treatment of vascular birthmarks, primarily port-wine stains and capillary malformations. This laser is also used to treat infantile hemangiomas (including residual changes and ulceration), spider angiomas, and pyogenic granulomas. Additionally, lasers have become a critical component in the treatment of scars resulting from burns, trauma, surgery, and inflammatory conditions. Apart from vascular lasers, such as PDL, ablative lasers, such as the fractional CO_2_ laser, are used to improve the size, texture, symptoms, and functional limitations caused by scars.

Though it is an effective and important treatment modality in pediatric dermatology, laser therapy is often associated with significant pain for the patient [1,2]. Pain associated with laser procedures is typically described as a heat or burning sensation. PDL is described as feeling like a hot rubber band snapping on the skin with each pulse [3], and the laser pulses 15 to 100 times per treatment session [4]. Infants and young children may require some form of anesthesia [3], and even adolescents and adults may have difficulty tolerating the procedure [5].

It is vital to mitigate pain and anxiety during laser procedures in pediatric patients. Unrelieved pain during pediatric procedures has been associated with adverse effects on recovery and postoperative behavioral abnormalities [6-8], including postprocedural symptoms of posttraumatic stress disorder [9]. Anxiety and pain can lead to a lack of cooperation with the procedure by the patient, which may impact the effectiveness of the therapy [5]. Darkness from laser eye protection and pain-related distress may also precipitate phobic responses in the patient [4], which increases their anxiety and can negatively impact subsequent treatments [10], as well as future interactions in health care settings [11]. Experiences of undertreated pain can have significant adverse effects on immediate and long-term mental health for pediatric patients [12]. Therefore, effective pain mitigation during pediatric laser procedures is a crucial component of biobehavioral intervention targeting pediatric patients.

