### Participant Timeline

Study enrollment at NCH—patients will be recruited prior to their first sequential dermatologic laser procedure. After consent and assent (if applicable) are obtained, patients will be randomized to either the VR-PAT intervention or the control group. A research associate will collect background information, such as demographics, anxiety levels, and prior video game experience, before randomization. VR-PAT instructions will be provided to the intervention group prior to participation.

Laser procedures at NCH (n=2 visits)—patients will receive their laser procedure as usual. Participants in the intervention group will wear the Pico headset and play the VR-PAT during their procedure. Participants in the control group will receive their laser procedure while wearing the VR headset (without the game). A researcher in the laser treatment room will observe the procedure and document, for the intervention group, the amount of time spent playing the VR-PAT, whether the participant declined to use it, and the number of interruptions of VR. Following the procedure, a different researcher (blinded to the group) will ask both groups of participants about their pain experience and satisfaction with the game. This process will be repeated once for each participant, as they will cross-over to the opposite intervention group at their next laser procedure.

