### Intervention

VR-PAT is the intervention for this RCT. VR-PAT is a standalone mobile health tool developed at NCH and does not require an internet or WiFi connection. The intervention is hosted on a Pico Neo 3 Pro Eye, which is a standalone VR headset that supports native eye tracking, enabling applications to gather real-time user feedback for behavior-based application control. Our VR game is the only application available on the headset and starts immediately upon pressing the power button, which ensures all participants play the VR game intended for this study.

During the laser procedure, participants will play the virtual game by slightly tilting their heads, thereby minimizing interference with the procedure while cruising on a boat and aiming for the snow-blowing statues floating along the riverbank. The statues will burst and emit snow if the participant correctly aims at them, and a thermometer placed at the front of the boat will show decreased temperatures as more snowflakes are blown. As feedback to reinforce continued engagement, a scoreboard placed beside the thermometer will show participants the number of statues they have activated. Additionally, as the temperature drops, snow and ice will start piling up on the boat and its surroundings, providing an enhanced “cooling” experience for dermatology patients. Audio from the headset provides surrounding and directionally-adaptive effects to match the progress of the game and the direction in which a participant’s head is turning, further enhancing the immersive experience of VR-PAT during dermatologic laser procedures. The active VR-PAT game can last indefinitely, so it can be used for the entire procedure without interruption.

Participants playing the VR will be advised to discontinue using the headset during a procedure if it causes motion sickness, headaches, nausea, or dizziness. The dermatologist will pause the laser procedure and switch the eye protection to one available in the outpatient clinic. Any adverse events resulting from participation will be noted and reported in the participant surveys.

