The comparator, or control, for this study is the same VR headset without the game, displaying only a dark screen. This comparator was chosen to maintain the experience of wearing something on the face for both groups. Patients undergoing a laser procedure are required to wear eye protection, which can include adhesive eye patches that occlude the eyes and create a similarly dark environment.

Participants in either intervention will be allowed to use any pain or anxiety medication that the dermatologist deems appropriate. Any medications provided will be documented.

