#### Participant Data (Self-Reported)

Prior to randomization, participants will report their prior video game experience, including the type of video games played, frequency, and favorite games. Before the laser procedure, all participants (control and intervention visits) will self-report their anxiety state using the State-Trait Anxiety Inventory for Children [32] (ratings ranging from “not at all” to “very much”) and their current anxiety using the Numeric Rating Scale (NRS; 0‐10) [33]. After the procedure, the participants will answer the remaining survey questions assessing overall pain score (NRS 0‐10) [34,35], worst pain score (NRS 0‐10), time spent thinking about pain (NRS 0‐10), length of the procedure (in minutes), and anxiety during the laser procedure (NRS 0‐10). Those playing the VR-PAT game will report their experience with the VR game (degree of realism, fun, engagement, and satisfaction; NRS 0-10) and respond to qualitative questions about their preferences with the VR-PAT. Participants will also be asked to report any simulator sickness associated with the VR game and whether they would want to use the VR again for future laser visits outside of research. These data will be collected at each of the 2 laser procedure study visits.

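### Symptoms are actively solicited only at VR visits and only as effects of the game, so symptom rates have no control-visit counterpart although both conditions wear the same headset

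*Protocol article*

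**What the plan says.** Safety is part of the overall objective, and the central hypothesis includes that VR-PAT is safe (Objectives).

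- **Solicited question.** Adverse Events and Oversight states who is asked and in what words: "Participants playing the VR-PAT game will be asked to answer the question, “Did the game make you feel not well? If yes, please explain".
- **Simulator sickness.** Participant Data (Self-Reported) ties this item to the game: "Participants will also be asked to report any simulator sickness associated with the VR game". The Abstract's Methods paragraph also assigns it to those playing VR-PAT.
- **Declines and interruptions.** Under Participant Timeline the observing researcher is to "document, for the intervention group, the amount of time spent playing the VR-PAT, whether the participant declined to use it, and the number of interruptions". Observed Measures repeats this for VR-PAT only.
- **Advice on symptoms.** Intervention addresses the same people: "Participants playing the VR will be advised to discontinue using the headset during a procedure if it causes motion sickness, headaches, nausea, or dizziness".
- **Control condition.** Intervention defines it: "The comparator, or control, for this study is the same VR headset without the game, displaying only a dark screen". Background and Significance presents the headset as eye protection as well as a distraction.
- **Routes open to everyone.** Every participant receives a telephone number for reporting adverse events, and coordinators review the collected data for reported events (Adverse Events and Oversight). Intervention adds a general sentence that events arising from participation will be noted, but it closes a paragraph about participants playing the VR and points to the participant surveys.

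**The concern.** Symptoms such as nausea, dizziness and headache can come from the game. They can also come from pain, medication, the laser procedure or wearing a headset, and all of these are present at the control visit. Asking only at the VR visit, and asking whether the game was the cause, leaves attribution to participants who may be as young as 5 and gives no background rate to set beside the answer.

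Some hazards belong to the headset and not to the game. The article says that little is known about the safety of VR headsets during laser procedures (Gap in Knowledge), and it warns: "Darkness from laser eye protection and pain-related distress may also precipitate phobic responses in the patient". A question about the game would not reliably bring out an eye complaint or a problem with headset fit at either visit. A headset removed during a control visit has no described place in the log.

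At stake is how the safety result can be read. Adverse events, including simulator sickness, are a feasibility measure, and the results are meant to inform a multisite study. A symptom rate seen at VR visits alone could be blamed on the game when it is background, or dismissed as background when the game is the cause.

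**Working it through.** The plan gives no figure to reproduce: the sample of 40 rests on budget and patient volume (Sample Size). The check is therefore mainly textual, with three illustrative calculations.

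**1. What is collected in each condition, as described**

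| Item | VR visit | Control visit |
|---|---|---|
| Felt unwell question | asked, as an effect of the game | not described |
| Simulator sickness | asked, tied to the game | not described |
| Decline, interruptions | logged | not described |
| Eye or headset complaints | not specifically asked | not specifically asked |
| Anxiety during the procedure (NRS) | yes | yes |
| mYPAS, three time points | yes | yes |
| Telephone line for adverse events | yes | yes |
| Study headset worn | yes | yes |

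One sentence might seem to fill the gaps in the right-hand column. The survey paragraph ends: "These data will be collected at each of the 2 laser procedure study visits". It covers the survey as a whole. The simulator-sickness item within it concerns the game, and Randomization and Blinding says that participants in the control condition cannot answer the VR experience questions. The sentence does not turn a game-specific item into a control-visit item.

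**2. Share of visits with a solicited question**

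Results reports 44 participants at the first visit and 40 at both.

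- Completers: 40 VR visits out of 40 + 40 = 80, so 40/80 = 50%.
- All attended visits: 44 + 40 = 84. The condition of the four non-completers at their only visit is not stated, so VR visits number 40 to 44. The share is 40/84 = 48% to 44/84 = 52%.

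**3. What a background rate alone would produce at VR visits**

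The documents give no background rate, so a range is assumed. With n = 40 VR visits and rate p per visit, the expected count is 40p and P(at least one report) = 1 − (1 − p)^40.

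| Assumed p | Expected reports | P(at least one) |
|---|---|---|
| 1% | 0.4 | 33% |
| 2% | 0.8 | 55% |
| 5% | 2.0 | 87% |
| 10% | 4.0 | 99% |

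Over much of this range some reports are likely even if the game adds nothing. The VR count alone cannot tell these cases apart.

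**4. What a paired question would have given**

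With 40 pairs, a true difference near zero and a proportion d of discordant pairs, the 95% half-width for the difference in symptom rates is about 1.96 × √(d/40).

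- d = 5%: 1.96 × √(0.05/40) = 6.9 percentage points
- d = 10%: 1.96 × √(0.10/40) = 9.8 percentage points
- d = 20%: 1.96 × √(0.20/40) = 13.9 percentage points

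The values of d are assumptions. The comparison would be descriptive, but it would be a comparison.

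**The case against.** Four stronger readings are tempting, and the documents do not support them.

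- **Control-visit harms go unrecorded.** A reader might infer this, but a researcher is in the treatment room at each procedure, all participants have a number to call, and reported events are discussed weekly. A volunteered control-visit event can be recorded. The fault is unequal solicitation.
- **Panic in the dark is never measured.** It is. Participants rate anxiety during the procedure at both visits, and mYPAS is scored three times at each procedure and compared between conditions as a primary outcome. The risk named in the Introduction therefore has both a measure and a comparator. What remains uncovered is headset removal and physical symptoms.
- **The safety objective fails for want of a comparator.** The scale-up criterion in Feasibility Outcomes is absolute (no serious adverse events), and no between-condition safety analysis is promised. That criterion needs no control rate, although it still depends on events being reported. The comparator is missing for solicited symptoms only.
- **Eye safety is left unexamined.** It rests on third-party testing of the headset for PDL and CO2 lasers and on the exclusion of diode laser use (Settings and Participants), not on event counts in 40 people.

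It can also be said that simulator sickness is expected from a moving game, so asking at VR visits is natural in a pilot. That is a good reason to ask there, but not a reason to ask only there or only about the game. Finally, the article condenses a full protocol that is not shown, and the forms may hold more. This stands as a caution. The article nevertheless states who is asked and quotes the question, so the point is about what it fixes and not about an omitted detail.

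**Conclusion.** The point holds for solicited symptoms and for the headset log. As described, these are obtained at VR visits only and attributed to the game, while control visits with the same headset rely on volunteered reports. About half of attended visits (48% to 52%) carry a solicited question, and the resulting symptom rate can be neither compared between conditions nor separated from effects of the procedure, medication or headset wear.

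The weight is moderate. The pain and anxiety comparisons are untouched, and so is the form of the scale-up criterion. What is limited is any statement that the game adds few symptoms, or none, relative to the control condition. The conclusion assumes that the article describes the solicited items fully. The background and discordance rates used above are assumptions and serve only to show scale.

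**What to change.** **This trial.** Data collection ended in November 2025, so only the reporting can change. If the forms hold no further solicited items, describe the symptom rate as uncontrolled and game-attributed, say that control-visit events came from spontaneous reports, and draw no conclusion on relative safety. Count all attended visits, including those of the four participants who did not complete both. This costs a few sentences in the results paper.

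**The planned larger study.**

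- Ask every participant one identical, neutrally worded question about symptoms (including eye symptoms) and headset problems at both visits.
- Place it before the question that reveals to the assessor whether the game was played. Game-specific items can follow.
- Log headset removals and interruptions in both conditions.
- Tabulate the answers by condition as a descriptive paired comparison, with all attended visits included.

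The cost is a slightly longer survey and more minor events to record and review. No extra visit is needed.

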### Sample Size

Since this is a pilot study, the focus of the statistical analysis will be on estimating the effect sizes of VR-PAT and their 95% CI, as well as the variances of the outcome measures. These findings will facilitate sample size calculations and study power estimates for future larger-scale randomized trials. We decided on a sample of 40 participants and 2 research visits based on the grant budget and the patient volume for the 1 dermatologist collaborating on this study.

Across acute pain studies, clinically meaningful improvements are generally larger than a 1-point change on the NRS 0‐10, with systematic review evidence suggesting minimum clinically important differences of approximately 13% to 36% reduction, with a median of 23% (IQR 18%-36%), corresponding to roughly 1.4‐2.3 points on the NRS [38,39].

### Data Analysis

To achieve aim 1, composite scores will be calculated for each laser procedure, encompassing the pain score, pain medication use during the procedure, and whether rescue medication was used. The rationale for choosing the composite score as the outcome is that prior researchers have shown a significantly high positive relationship between pain medication use and self-reported pain scores [40]. From a clinical perspective, pain scores alone are influenced by the patients’ actual opioid use and may not fully reflect the treatment benefit of VR [41]. The composite score approach, therefore, provides a single, patient-centered outcome that represents overall analgesic benefit, aligning with the goal of achieving adequate pain control while minimizing opioid exposure. In our analysis, we will apply the rank-based approach by Dai et al [40] to assign weights to pain and medication use, reflecting their complementary clinical importance as measures of pain reduction [41]. In the primary analysis, the composite scores from the laser procedure with VR will be compared to those from the procedure with standard care (ie, control) using paired 1-tailed *t* tests or the Wilcoxon signed rank tests (depending on the distribution of the composite scores) due to the cross-over design. The clinical effect size will be the mean difference (if paired *t* tests are used) or median difference (if Wilcoxon signed rank tests are used) in the composite score between VR and control procedures. The SD of the difference will also be calculated.

For aim 2, the mYPAS score had 6 repeated measurements over time (T0, T1, and T2 during each of the 2 laser procedures). At the first procedure, we will compare the change in mYPAS scores from T0 to T1 and T0 to T2 between the control and VR groups using either 2-sample 1-tailed *t* tests or the Wilcoxon rank sum tests (depending on the distribution of the change in mYPAS scores). The clinical effect size will be the difference in medians of the change in mYPAS, with the confidence limits calculated by bootstrapping with replacement using 1000 repetitions. Bootstrapping has been found to provide better confidence limits with asymmetric data, such as the mYPAS score in our study, and is the recommended method. The same statistical analysis approach has been successfully used by other researchers, who reported that VR effectively reduced preoperative anxiety among 71 children aged 5 to 12 years scheduled for elective surgery [42]. At the second procedure, we will compare the mYPAS scores at T0 and T1 between the control and VR groups using the Wilcoxon rank sum tests since mYPAS scores are shown to be asymmetric [42]. The clinical effect size will be the difference in medians of mYPAS. Confidence limits will be calculated using bootstrapping again.

Linear mixed-effects models with participant-specific random intercepts will be fit on the composite scores to evaluate any modification of the effects of VR on pain by sex, age, and anxiety, with adjustment for baseline covariates and potential carryover effects of VR from the first to the second procedure. The following covariates will be included in the regression models: study group (VR vs control), period (second vs first procedure), study group by period interaction (test for carryover effect), age, age by study group interaction, sex, sex by study group interaction, procedural anxiety, procedural anxiety by study group interaction, race, ethnicity, State-Trait Anxiety Inventory for Children, 6-item State-Trait Anxiety Inventory, and average mYPAS scores between T0 and T1. We will include each of the 3 interaction terms in a separate regression model. Due to the limited sample size, testing the interaction may not be feasible. The study will then run the main linear models without interaction terms. The results will provide us with preliminary data to estimate the future study sample size and power. In case a significant carryover effect is detected, we will use only data from the first procedure to evaluate the VR effect using 2-sample *t* test or Wilcoxon rank sum tests (depending on the distribution of the composite scores).

All statistical analyses will follow the intention-to-treat principle, wherein participants will be analyzed according to their assigned study groups, regardless of compliance status or group switching during the study.

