### Randomization and Blinding

A block randomization scheme with a block size of 4 will allocate participants to 1 of the 2 intervention sequences (VR-PAT followed by control or control followed by VR-PAT) at a 1:1 ratio without stratification. We chose a block randomization strategy to avoid imbalances in allocation to the intervention at the first visit in case we were unable to recruit our planned sample. The randomization scheme was developed and uploaded to a study-specific REDCap (Research Electronic Data Capture; Vanderbilt University) project by the project manager. Study participants are randomized into intervention sequences after signing consent and completing the baseline survey. Research recruiters and participants are not aware of the intervention assignment until the participant is randomized in REDCap.

We cannot blind the participants or the clinical team to the assigned intervention since the headset will either be turned on or off. The researcher who randomized the participant and observed the laser procedure will not be blinded, but a second researcher, who is blinded to the intervention group, will collect pain ratings and anxiety post procedure. The second researcher will wait in a different room during randomization and the laser procedure, and the first researcher will remind the participant at the end of the laser procedure to keep their group a secret until they are asked. The study biostatistician will also be blinded to the intervention group while performing analyses on the primary outcome. The data will be blinded by removing labels such as “VR” and “Control” and replacing them with unidentifiable letters (eg, “A” and “B”). The biostatistician will need to be unblinded for secondary outcomes, as only participants in the intervention group will answer the VR experience questions.

The blinded researcher will need to be unblinded after pain and anxiety ratings are obtained, as those in the control environment will not be able to answer the VR experience questions. The researcher will become unblinded by asking participants whether they played the game. The biostatistician will also be unblinded for full analyses by being provided with the full dataset, including complete data labels and VR questions. This unblinding will take place after the primary outcome analysis has been completed.

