This study is subject to some known limitations. First, all the participants come from the same hospital, and all the laser procedures are performed by the same physician, which limits our ability to generalize the findings. Second, since complete blinding was not possible due to the nature of the intervention, there is a chance of expectation bias among participants and clinicians. The research team attempted to manage participants’ expectations at recruitment and prior to each visit by explaining the research nature of the VR. A choice was also made not to measure participants’ expectations for the VR because we felt that this would prompt a reflection on their expectations and peak excitement. The third limitation is in evaluating the possible sample size. There has been more loss to follow-up than anticipated due to patients not following up clinically. This limits the ability to retain them in this research study. The proportion of eligible participants who were recruited is also lower than expected. This is largely related to many screened patients not ultimately scheduling a laser procedure. This will be a consideration for future studies in determining the number of physicians and/or sites needed to complete a powered study.

The future research direction, following the successful completion of this study, depends on the results but could include a fully powered efficacy study and, eventually, a multisite implementation study. In designing future implementation and dissemination work, sustainability will be a priority. This will include evaluating insurance reimbursement to cover the cost of owning and using this VR. We would follow in the footsteps of companies like AppliedVR, which was the first VR to obtain US Food and Drug Administration–authorization and established a unique Healthcare Common Procedure Coding System Level II code [44].

In conclusion, patients needing outpatient laser therapy have unique needs for pain and anxiety management, particularly in the context of ocular protection from laser damage. VR is a promising digital technology that can improve the experience of patients requiring dermatologic laser therapy. We anticipate that findings from this innovative randomized clinical trial will provide early evidence on the efficacy of VR-PAT in reducing self-reported pain and anxiety during outpatient laser procedures.

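### The primary pain composite includes medication chosen by an unblinded dermatologist, and no rule stops a medication-only difference being read as less pain

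*Protocol article*

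**What the plan says.** Data Analysis, aim 1, builds a score for each procedure "encompassing the pain score, pain medication use during the procedure, and whether rescue medication was used". It uses a rank-based method "to assign weights to pain and medication use, reflecting their complementary clinical importance as measures of pain reduction", and the test is assigned to this score: "In the primary analysis, the composite scores from the laser procedure with VR will be compared to those from the procedure with standard care", by a paired 1-tailed t test or the Wilcoxon signed rank test. The effect size and the SD of the difference are also defined on the composite. The mixed models later in the section are fitted to the composite in order to study VR's effects on pain, and the Abstract uses the composite to evaluate pain reduction.

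Primary Outcomes is different. Its pain outcomes are self-reported worst pain, average pain and time spent thinking about pain, each on a 0–10 scale, compared between VR and control visits. Medication is not among them.

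On who decides medication, Intervention says "Participants in either intervention will be allowed to use any pain or anxiety medication that the dermatologist deems appropriate". On blinding, Randomization and Blinding says "We cannot blind the participants or the clinical team to the assigned intervention since the headset will either be turned on or off", and adds that "a second researcher, who is blinded to the intervention group, will collect pain ratings and anxiety post procedure". The Discussion says that one physician performs all the laser procedures, and concedes that "there is a chance of expectation bias among participants and clinicians".

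**The concern.** Two of the three parts of the primary score, medication use and rescue use, depend on decisions made by someone who knows the condition. The blinded researcher collects ratings, and the blinded biostatistician analyses them; neither blinds prescribing. With a single prescriber, a habit that differs between VR and control visits does not average out across clinicians.

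The composite's rationale is that medication use and pain scores are related, so that either alone may miss part of the benefit. That is reasonable while medication responds to pain. It fails to the extent that medication responds to knowledge of the condition. The composite can then differ between visits although VR has done nothing to pain.

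The consequence is in the conclusion. The article promises early evidence on self-reported pain, and the pilot's effect estimates are meant to size later trials. Followed as written, the plan would let a difference arising only from medication be reported as pain reduction and carried into the next design.

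**Working it through.** **Inputs from the article.** 40 participants with both visits; a composite of pain, medication and rescue use; paired 1-tailed test. No significance level, medication rate, rescue rate or numeric weight is given, and no power figure is stated that could be reproduced.

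**Assumptions.** 5% level; NRS pain mean 5, SD 2.2, within-person correlation 0.5; VR has no effect on pain; medication scored yes/no; ranks pooled over both visits; each component expressed as (rank − mean rank)/mean rank, equally weighted. Rescue is left out at first.

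**Shift caused by prescribing.** With 80 pooled visits, users and non-users differ in mid-rank by 80/2 = 40, and the mean rank is 81/2 = 40.5. One change of medication status therefore moves the score by 40/40.5 = 0.988. A 10-point gap shifts the mean composite by 0.10 × 0.988 = 0.099, and a 20-point gap by 0.198, whatever the base rate.

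**Approximate rejection rate, 30% control v 20% VR.**
- Pain part of the variance of the difference: 2 × (1/3) × (1 − 0.48) = 0.347. Ranks scaled to about −1 to 1 have variance 1/3, and a correlation of 0.5 becomes a rank correlation of about 0.48.
- Medication part, taking use as independent between visits: 0.988² × (0.30 × 0.70 + 0.20 × 0.80) = 0.976 × 0.37 = 0.361.
- SD = √0.708 = 0.841; SE = 0.841/√40 = 0.133; shift/SE = 0.099/0.133 = 0.74.
- Probability of favouring VR ≈ Φ(0.74 − 1.645) ≈ 18%.

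For 40% v 20%, the variance is 0.347 + 0.976 × 0.40 = 0.737, the SE 0.136 and the ratio 1.46, giving Φ(1.46 − 1.645) ≈ 42%. For 20% control v 30% VR the shift changes sign: Φ(−0.74 − 1.645) ≈ 1%.

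**Simulation, same set-up.** Ranges cover separate runs. Entries are the percentage of trials in which the composite favours VR.

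| Medication use, control v VR | Medication does not affect pain | Medication lowers NRS by 1.5–2 points |
|---|---|---|
| 30% v 30% | 5% | – |
| 30% v 27.5%, or 5% v 2.5% (one visit in 40) | about 8% | – |
| 30% v 25%, or 10% v 5% (two visits) | 11–12% | – |
| 30% v 20% (four visits) | 17–20% | 12–15% |
| 40% v 20% (eight visits) | 41–46% | 26–32% |
| 20% v 30% (more at VR visits) | 0.5% | about 1% |

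In a variant with pain mean 4 and SD 2.5, 30% v 20% medication use gave 19%, and adding rescue use of 15% v 10% as a third component raised this to 27%. The Wilcoxon test gave results within about 5 percentage points of the t test.

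**NRS pain tested alone.** It favours VR in about 5% of trials at every gap if medication does not affect pain. If medication relieves pain, it does so in about 2% or fewer at the 10- and 20-point gaps with less medication at VR visits, and in 10–12% with more (20% v 30%). The ratings are therefore not immune to prescribing either.

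**The case against.** **Much of the reporting is already promised.** Primary Outcomes says the NRS items will be compared between conditions, Sample Size says the focus is on effect sizes with 95% CIs, and the Abstract says medication usage will be calculated per visit. A reader might infer that the components will go unreported; the article does not support that. What stands is that Data Analysis defines the test and effect size only for the composite, reads it as pain, and says nothing about components that disagree. Detailed methods for each component may sit in a fuller plan, but how the composite is interpreted is stated here.

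**Less medication at equal pain is a benefit.** Data Analysis presents the composite as overall analgesic benefit, so a medication difference driven by need is not a false positive. This is correct. The result misleads only if prescribing follows knowledge of the condition, or if the composite is reported as self-reported pain.

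**The size is assumed.** It is. If medication is rare, or settled before the condition is known, the effect is small. At the second visit, however, the crossover makes the condition known in advance. A reader might also infer that the composite is biased towards VR; nothing in the article fixes the direction.

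**The NRS is not a protected measure.** A reader might treat the blinded researcher as securing the ratings. That researcher only collects them; they come from participants who know their condition.

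**It is a disclosed limitation in a pilot.** Expectation bias among clinicians is admitted, though not linked to the composite, and none of the scale-up thresholds uses the composite. This limits the consequences but does not settle how the pain result should be worded.

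**Conclusion.** The concern holds as a problem of interpretation in the primary pain analysis. The composite is tested as primary and read as pain, the listed primary pain outcomes are NRS items only, and two components depend on one unblinded prescriber. With no VR effect on pain, 40 pairs, equal rank weights and a 1-tailed 5% test, the chance of a result favouring VR rises from 5% to about 8–12% for a gap of one or two visits, 12–20% for 30% v 20% and 26–46% for 40% v 20%. The low ends of the last two ranges apply if medication itself relieves pain. With the gap reversed, the composite favours VR in about 1% of trials and could conceal a benefit.

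All the rates are assumptions. The article does not show that prescribing differed between conditions, so these figures say what can happen, not what did. The point is worth fixing but does not argue against having a composite.

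**What to change.** Keep the composite as a measure of overall analgesic benefit, and add to Data Analysis:

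1. Each NRS pain item in Primary Outcomes gets a paired VR–control estimate with 95% CI.
2. Medication use and rescue use are each compared by condition as separate paired summaries.
3. A composite difference that arises only from medication is reported as a difference in medication use, not as reduced self-reported pain.
4. A statement that NRS ratings come from unblinded participants and can themselves be affected by medication, so these steps close the prescribing route only.
5. A statement that the rule was added after data collection ended in November 2025 but before the blinded primary analysis, if that still holds. If it does not, say so.

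The cost is a few lines of text and some paired summaries of outcomes the plan already uses. The downside is that a positive result on the composite alone no longer supports a pain claim. No medication rule is changed.
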